### 3.3 Study design

This study is a pilot single-site randomized sham-controlled interventional clinical trial based at the Interventional Psychiatry Program, St. Michael’s Hospital – Unity Health Toronto (UHT) in Toronto, ON, Canada. The trial will compare a course of 10 sessions of 130 Hz tTIS stimulation vs. 10 sessions of sham stimulation, delivered over 2 weeks (Figure 1). Thirty participants with MDD will be recruited into the trial and randomized into two parallel arms (active tTIS vs. sham) in a 1:1 fashion. Block randomization will be stratified by sex to allocate participants using a secure randomization module on Research Electronic Data Capture (REDCap) (Harris et al., 2009), as sex differences in brain volume and skull anatomy influence NIBS treatment outcomes (Hanlon and McCalley, 2022). Participants, investigators, outcome assessors, and data analysis will be blinded to treatment allocation. A randomization table will be generated using an external tool and uploaded to REDCap. Once a new participant is ready to be randomized, a research coordinator external to the study will enter their sex (a stratification variable) into REDCap, and the system will use the pre-defined randomization table to assign them to a treatment group.

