### 3.4 Sample size considerations

Based on studies in TES with fMRI, block design, and use of computational iterative neurostimulation (Ghobadi-Azbari et al., 2021), we expect that 30 participants will have adequate power to demonstrate target engagement of the sgACC. The proposed sample size (*n* = 30) is also based on the overall goal of (a) reasonably assessing the feasibility outcomes and (b) estimating the variability of the clinical outcome measures and is consistent with published recommendations for pilot trials designed to estimate standard deviations for larger future randomized controlled trials when the effect size is small-to-medium (Lancaster et al., 2004; Whitehead et al., 2016). As such, based on sample sizes used in pivotal TES studies (Berlim et al., 2013), we expect that 30 participants will be adequate to demonstrate the feasibility, tolerability, safety, and therapeutic effect of tTIS. Moreover, the pilot study will provide effect size estimates to design a definitive efficacy trial.

For this pilot study, to have a 90% power (i.e., being 90% confident that the effect is true and that it is not a type I/II error), the top end of the two-sided 95% confidence intervals will be the maximum confidence of having a true difference between active tTIS and sham arms. If there is no difference between active tTIS and sham arms, then *p* ≥ 0.051 will indicate no difference with a 90% confidence, and if there is a difference, then *p* ≤ 0.05 will indicate the difference with a 90% confidence. To have the medium effect size of *f* = 0.25 for the mixed-model analysis of variance (Cohen, 2013), 30 patients (15 per group) are required to have a 90% power. We anticipate having a 15% dropout rate in the randomized phase of the study due to side effects or lack of adherence to protocol and approximately a 50% response rate in the acute phase of treatment. A sample size of 15 per group will give us precise estimates of variability in the clinical outcome, namely a change in the Hamilton Depression Rating Scale 17-Item (HAM-D-17) (Hamilton, 1960) score over time (Korn et al., 2012; Cohen, 2013), and this sample size is within the recommended total sample sizes for a precise estimate of the standard deviation and correlation for HAM-D-17 scores to use in the future sample size calculation for a definitive larger scale trial (between *n* = 24 and 50) (Julious, 2005; Sim and Lewis, 2012; Billingham et al., 2013).

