### 3.10 Magnetic resonance imaging

At Visits 1 and 10 (baseline vs. post-treatment), participants will undergo a 60-min MRI (Siemens 3.0 T Skyra) session with a structural and functional protocol using a 32-channel head coil. The MRI protocol comprises: (1) a high-resolution T1-weighted anatomical scan acquired using a magnetization-prepared rapid gradient-echo (MP-RAGE) sequence; (2) a series of B_0_ field map scans to correct the images for signal distortion; (3) fMRI images using a whole-brain T2*-weighted BOLD echo-planar imaging series during the awake resting-state in the eyes-open condition and while viewing a fixation cross (Raichle and Snyder, 2007); (4) a whole-brain diffusion-tensor imaging series; and (5) a 3D pseudo-continuous arterial spin labeling (pCASL) scan. Cardiovascular and respiratory data will be monitored throughout the entire session and used to correct for MRI signal distortions.

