### 3.12 Analysis plan

#### 3.12.1 Primary outcomes: target engagement

BOLD activation (power in the 0.015–0.08 Hz frequency range), CBF, seed-based resting-state FC, and anatomical connectivity of the sgACC will be the primary outcome measures to demonstrate sgACC target engagement with a course of tTIS. We hypothesize that we will observe an increase in the BOLD activation and CBF in the sgACC voxels in the tTIS arm but not the sham and an increase in resting-state FC between the sgACC and bilateral dlPFC, vmPFC, and insula in the tTIS arm but not the sham. We also hypothesize that changes in the resting-state FC will be associated with changes in anatomical connectivity between the sgACC and the abovementioned brain regions. Additional exploratory analyses of changes in the whole-brain FC of the sgACC and their association with anatomical connectivity will be performed.

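### The 90% power figure for 30 patients makes no allowance for the 15% dropout the plan expects, and it names no outcome, number of occasions or correlation

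*Protocol article*

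**What the plan says.** Section 3.4 (Sample size considerations) makes two separate statements about power. For the imaging objective it gives no number: "we expect that 30 participants will have adequate power to demonstrate target engagement of the sgACC". Later in the section comes the only numerical calculation, at a medium effect of f = 0.25 in a mixed-model ANOVA: "30 patients (15 per group) are required to have a 90% power". It is introduced as applying to the pilot study as a whole and framed as a comparison of active tTIS with sham. The two-sided 5% level follows from its reference to "the top end of the two-sided 95% confidence intervals". No outcome, number of repeated measurements or correlation is attached to it.

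The next sentence begins: "We anticipate having a 15% dropout rate in the randomized phase of the study". Section 3.3 sets enrolment: "Thirty participants with MDD will be recruited into the trial and randomized into two parallel arms (active tTIS vs. sham) in a 1:1 fashion".

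Section 3.12.1 makes the MRI measures primary, and section 3.10 fixes two scans: "At Visits 1 and 10 (baseline vs. post-treatment), participants will undergo a 60-min MRI". Table 2 schedules HAM-D-17 five times: baseline and Visits 5, 10, 11 and 12. Three of these fall at or before Visit 10, which section 3.8 names as the primary time point.

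Section 3.4 also says how p-values will be read: p of 0.051 or more is to indicate no difference between arms, with 90% confidence.

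**The concern.** The number said to be required for 90% power equals the number randomized, while the same paragraph expects to lose 15% of them. By the plan's own assumption the requirement will not be met.

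The figure also cannot be checked as printed. In a repeated-measures design, power at a fixed f depends heavily on how many occasions are analysed and how strongly they correlate, and the paragraph gives neither. A reader will naturally apply 90% to the primary question, which rests on two scans.

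The rule for p ≥ 0.051 gives the figure practical weight. It turns the power claim into a reading of a null result. If power is really 0.67 to 0.75, a true effect of the assumed size would be missed 25% to 33% of the time, yet would be reported as no difference with 90% confidence.

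**Working it through.** **Inputs from the article.** f = 0.25; two-sided alpha 0.05; N = 30, 1:1; dropout 15% (section 3.4 and section 3.3). MRI occasions: 2 (section 3.10). HAM-D-17 occasions: 3 up to Visit 10, 5 in all (Table 2).

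**Assumptions, because the article gives no figure.** Correlation ρ between occasions, with 0.5 as the reference value and a range shown; sphericity.

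**Completers.** 30 × 0.85 = 25.5, so 25 to 26.

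**Formula.** For the group × time interaction with two groups and m occasions:
- λ = f² × N × m / (1 − ρ)
- df1 = m − 1
- df2 = (N − 2)(m − 1)
- power = P(noncentral F > the 95% point of central F)

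**Reproducing the plan's figure.** With m = 4, ρ = 0.5, N = 30: λ = 0.0625 × 30 × 4 / 0.5 = 15.0, df 3 and 84, power 0.903. Here 30 is the smallest N that reaches 90%. Other settings also reach 90% at N = 30: three occasions at ρ = 0.6 (0.915), five at ρ = 0.5 (0.943), and two at ρ of about 0.67 (0.902).

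**Effect of dropout and number of occasions at ρ = 0.5.**

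| Occasions | λ at N = 30 | Power, N = 30 | Power, N = 25-26 |
|---|---|---|---|
| 2 (MRI) | 7.5 | 0.753 | 0.668-0.687 |
| 3 (HAM-D-17 to Visit 10) | 11.25 | 0.841 | 0.760-0.778 |
| 4 (reproduces the stated figure) | 15.0 | 0.903 | 0.834-0.850 |
| 5 (HAM-D-17, all visits) | 18.75 | 0.943 | 0.887-0.901 |

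**Two scans over a range of correlations.**

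| ρ | Power, N = 30 | Power, N = 25-26 |
|---|---|---|
| 0.3 | 0.61 | 0.53-0.54 |
| 0.5 | 0.75 | 0.67-0.69 |
| 0.7 | 0.93 | 0.87-0.88 |
| 0.8 | 0.99 | 0.97 |

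Reaching 90% with two scans needs ρ of about 0.67 at N = 30, 0.72 at N = 26 and 0.73 at N = 25.

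**Cross-check for two scans.** With two groups and two occasions, f = 0.25 is a between-arm difference in change of 4 × 0.25 = 1.0 raw SD. The SD of change is √(2(1 − ρ)) raw SDs, which is 1.0 at ρ = 0.5. A two-sample t-test on change with 15 per arm then has noncentrality 1.0 × √(15 × 15 / 30) = 2.74. Its square is 7.5, the λ in the table, and its power is also 0.753.

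**Detectable difference, in SDs of change** (two-sample t-test, baseline to Visit 10). This form does not need ρ.

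| Evaluable per arm | 80% power | 90% power |
|---|---|---|
| 15 / 15 | 1.06 | 1.23 |
| 13 / 13 | 1.15 | 1.33 |
| 13 / 12 | 1.17 | 1.36 |

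**The case against.** The strongest reply is that the 90% was never claimed for MRI. It belongs to a mixed-model ANOVA, and the only group × time mixed model in the article is for the continuous clinical outcomes (section 3.12.2). MRI change is to be tested with paired tests (section 3.12.1), and its power is called adequate without a number. This stands. A reader might infer that the primary outcome misses its stated 90%, but the article does not expressly state 90% for that outcome. The two-scan shortfall also depends on an undisclosed correlation: at 0.8, power is 0.97 even after dropout.

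Second, the number is not an arithmetic slip. It reproduces exactly under a conventional setting. If it refers to the full five-visit HAM-D-17 course, about 0.89-0.90 survives the expected dropout, and section 3.12.2 does not confine the mixed model to Visit 10. This stands as well, so it would be wrong to say that four occasions is the one setting that supports 90%. A mixed model can also use partial data from dropouts, so completer-based figures for HAM-D-17 are somewhat pessimistic. That does not help MRI: with two scans, a patient without the second adds nothing to the estimate of change.

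Third, a reader might see a conflict between f = 0.25 and the mention of small-to-medium effects in section 3.4. That phrase describes recommendations for pilots that inform larger future trials. It is not this trial's assumed effect, so there is no contradiction.

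None of this answers the missing dropout allowance, or the use of 90% to read a null result.

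**Conclusion.** The point holds in a limited form. The dropout inconsistency follows from the article alone: 30 required, 30 randomized, 15% expected lost. In the setting that reproduces the stated figure most closely, power falls from 0.90 to 0.83-0.85.

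At that same correlation of 0.5, 90% is not reached for a group × time test on two scans or on HAM-D-17 up to Visit 10, before or after dropout. It is roughly kept for the five-visit HAM-D-17 course, provided follow-up loses no more patients. These figures rest on an assumed correlation and on sphericity. The MRI figures are for the between-arm comparison implied by the hypothesis of superiority to sham in section 2, not for the paired tests in section 3.12.1.

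If the 90% is not meant for MRI, the primary objective has no numerical power statement, and the claim of adequate power rests on cited literature alone. The rule for p ≥ 0.051 is unsupported on either reading. This is a correction to the reporting of power that should be made. It does not invalidate the design of a pilot whose stated purposes already include estimating variability and effect sizes.

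**What to change.** No additional enrolment is needed. Revise section 3.4 as follows:

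1. State power for 25 to 26 evaluable patients, naming the outcome, the number of occasions and the assumed correlation.
2. For the between-arm comparison of change from baseline to Visit 10, give the detectable difference: about 1.15-1.17 SD of change at 80% power and 1.33-1.36 SD at 90%.
3. Remove the statement that p ≥ 0.051 indicates no difference with 90% confidence. Report the estimated difference with its 95% confidence interval instead.
4. Replace the claims that 30 participants are adequate to demonstrate target engagement and therapeutic effect with wording that the trial will estimate them.

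The cost is rewriting one section, with a stated power that looks less favourable. No procedure, visit or patient number changes.

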### 3.5 Data and safety monitoring

Adverse Event (AE) data will be collected using a standard form at each visit. Additionally, a standard questionnaire for tTIS-related AEs will be completed before and immediately after each treatment session. If a participant indicates to experience intolerable side effects during stimulation, stimulation will be terminated immediately. If severe side effects are reported during or after stimulation in 2 consecutive sessions, or in more than 2 sessions, participation will be terminated. A Data and Safety Monitoring Board will be assembled to monitor participant safety and changes in clinical scores. This panel comprises two independent, external experts. REDCap software (Harris et al., 2009) will be used for data collection and management. Access will be secured by an encrypted virtual private network and protected by multiple levels of authentication. All other identifiable participant data will be stored on a secured internal server.

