### 3.6 tTIS stimulation paradigm

The tTIS intervention will be delivered using the High-Definition (HD) Interferential Neuromodulation System (IFS) manufactured by Soterix Medical, Inc. (Woodbridge, NJ, United States). The device is designed to deliver two independent alternating currents to the brain at different frequencies. tTIS will be delivered through two pairs of sintered ring HD electrodes (circular external diameter 1.2 cm) placed on the scalp via a 10-10 HD cap and an HD-GEL (Soterix Medical, Inc.), with each electrode pair delivering continuous high-frequency sinusoidal waveforms at frequencies of 1,000 and 1,130 Hz, respectively, resulting in a carrier frequency of 1,065 Hz and a “beat” frequency of 130 Hz. This stimulation paradigm was designed to mimic the frequency used in DBS of the sgACC for TRD (Mayberg et al., 2005; Khairuddin et al., 2020). The current amplitude will be 2 mA per electrode pair, i.e., the injected current will sinusoidally vary between 0 and 2 mA. The stimulation will be delivered for 30 min, which includes 30-s ramp-up and ramp-down periods at the start and end. For sham stimulation, the current will be ramped down to 0 mA directly after ramping up, mimicking the sensations associated with verum stimulation. Based on our prior experience, we expect to see impedances between 1 and 10 kΩ during stimulation, which is tolerated well by participants. If the impedance of any stimulation channel exceeds 25 kΩ, the stimulation device will give a warning, upon which the experimenter will add gel to reduce the impedance (without stopping the stimulation). If any impedance exceeds 50 kΩ, the channel quality indicator will display red, indicating that the impedance is outside of the preferred range. At this time, stimulation will not cease, and the reduced output current will be delivered in relation to the maximum compliance voltage of the stimulator.

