### 3.8 Study procedures

Participants will complete telephone pre-screening and, if eligible, will be invited to the hospital to undergo urine tests for the presence of pregnancy and substance use, which will be screened out. The screening will involve the review of eligibility criteria, demographics information, medical history, psychiatric history, treatment history, confirmation of MDD diagnosis and the presence of moderate-to-severe symptoms, and a review of safety considerations to receive rTIS or undergo an MRI. If all eligibility criteria are met, written informed consent will be obtained, and participants will be randomized into one of the treatment arms (active tTIS vs. sham). All participants will have 13 on-site visits: screening (Visit 0), baseline combined with day 1 of tTIS (Visit 1), days 2–10 of tTIS (Visits 2–10), and two separate follow-up visits after the last day of tTIS during weeks 3 (Visit 11) and 6 (Visit 12). Visits will be completed on weekdays (Monday to Friday) for compliance and convenience. At baseline (Visit 1) and the last day of tTIS (Visit 10), participants will undergo a 60-min MRI session for the assessment of sgACC target engagement; this session includes the acquisition of anatomical, resting-state functional, perfusion, and diffusion scans. At Visits 1, 5, and 10, resting-state and task-based EEG data will be collected for assessment of changes in brain oscillations that tTIS is likely to modulate (Esmaeilpour et al., 2021). Most clinical assessments will be completed at Visits 5 and 10 to reduce participant burden. The primary outcome time point will be Visit 10, corresponding to the time point at which post-treatment MRI and clinical assessments will be completed. Refer to Table 2 for the study schedule, clinical assessments, and study procedures conducted during each visit.

**TABLE 2 T2:** Proposed schedule of assessments and procedures.

	Study period													
	Enrollment	Baseline	Randomized treatment phase										Follow-up period	
			Week 1					Week 2					Week 3	Week 6
Visit	0	1	1	2	3	4	5	6	7	8	9	10	11	12

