T1-weighted and T2*-weighted images will be preprocessed, with steps including volumetric segmentation and surface extraction, normalization, motion correction, field unwarping, bias field correction, and brain extraction (Esteban et al., 2019). Preprocessing and denoising will be performed using tedana: TE Dependent ANAlysis v.23.0.1 pipeline^1^ (Kundu et al., 2012, 2013; DuPre et al., 2021), which includes slice timing correction, estimation of motion correction, spatial normalization, signal distortion correction, smoothing, and filtering. The left and right sgACC will be identified using the Desikan-Killiany (FreeSurfer) anatomical labeling scheme (Desikan et al., 2006). Pre- vs. post-treatment changes in sgACC time series properties, such as BOLD activity, will be assessed using Wilcoxon signed-rank tests or paired *t*-tests on signal variance at each sgACC voxel. pCASL scans will be used for perfusion detection using the BASIL toolset to conduct simple CBF quantification in the sgACC voxels (Chappell et al., 2009). In addition, seed-based resting-state sgACC FC maps will be computed by calculating Pearson correlation coefficients between the BOLD time series across the rest of the brain, with a focus on bilateral dlPFC, vmPFC, and insula, and the sgACC voxel-averaged seed time series. Using SPM12, 5 mm spherical seeds will be created around the sgACC MNI coordinates, and contrast analysis on the FC will be run using CONN Toolbox v.22a (RRID:SCR_009550, v.22a) (Nieto-Castanon and Whitfield-Gabrieli, 2021). FC-based target engagement will be defined as statistically significant pre- vs. post-treatment changes in these sgACC FC maps, as computed with mass univariate paired *t*-tests.

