#### 3.12.2 Secondary outcomes: clinical assessments

Improvement in depressive symptoms will be the main secondary outcome measure. Additional secondary outcome measures will include feasibility, safety, and tolerability metrics of rates of recruitment, withdrawals, and adherence, as well as the number and nature of AEs and serious AEs.

For continuous outcome measures, a mixed-effects model will be used to assess differences in the rate of improvement over time and the final outcome across groups. Treatment group, time, and treatment group × time interaction will be used as explanatory variables, with participant as a random factor. The significance of the treatment group × time interaction effect will be used to test the null hypothesis. For categorical outcome measures, response will be defined as a ≥50% reduction in HAM-D-17 and QIDS-SR-16 total scores at Visit 10. Remission will be defined as a HAM-D-17 total score of <8 at Visit 10. The two-tailed Chi-squared test will be used to assess the significance of any observed differences in the proportion of responders and remitters between groups.

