### 3.13 Early withdrawal and study termination

Participants are free to withdraw from the study at any time without penalty or loss of benefits. A participant will be discontinued if they miss more than three treatment sessions, are non-compliant, experience worsening depression, meet exclusion criteria at a later time point, experience severe side effects, or if the stimulation device is believed to be unsafe. This study may be terminated if there is sufficient reasonable cause.

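### Sections 3.5 and 3.13 give unreconciled thresholds for stopping a participant over severe side effects, and 3.5 ends participation rather than stimulation

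*Protocol article*

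**What the plan says.** Section 3.5 (Data and safety monitoring) has two rules. For intolerable side effects during a session, stimulation is stopped at once. For repeated severe ones: "If severe side effects are reported during or after stimulation in 2 consecutive sessions, or in more than 2 sessions, participation will be terminated".

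Section 3.13 (Early withdrawal and study termination) lists grounds on which a participant will be discontinued. They include those who "experience worsening depression, meet exclusion criteria at a later time point, experience severe side effects". No number of sessions is attached to the severe-side-effect item, and 3.5 is not mentioned. The list does open with a count for a different item: "A participant will be discontinued if they miss more than three treatment sessions".

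Three other sections show what depends on these rules:
- Section 3.12.2: "Additional secondary outcome measures will include feasibility, safety, and tolerability metrics of rates of recruitment, withdrawals, and adherence".
- Section 3.8, on the scans: "At baseline (Visit 1) and the last day of tTIS (Visit 10), participants will undergo a 60-min MRI session". Table 2 schedules no later MRI.
- Section 3.8, on timing: "The primary outcome time point will be Visit 10, corresponding to the time point at which post-treatment MRI and clinical assessments will be completed".

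**The concern.** A coordinator working from 3.13 alone would discontinue a participant after a single severe session. One working from 3.5 alone would have no instruction to do so until a second consecutive session or a third in total. This is a safety rule for a repeated course of a new stimulation method in patients, so staff need one threshold.

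The statistical consequence is that part of the withdrawal rate would reflect which section was followed rather than how well the treatment is tolerated. That rate is a secondary outcome of a pilot meant to give feasibility and tolerability estimates for a larger trial.

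The lesser matter is one word. In 3.5 the sentence on intolerable effects stops stimulation, and the next one, on severe effects, ends participation. Read literally, a participant who meets the 3.5 count before Visit 10 has no post-treatment scan for the paired pre/post comparisons in 3.12.1 and no Visit 10 ratings. The loss would fall on people who tolerate treatment poorly.

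**Working it through.** The article states no figure on this point to reproduce. The check is a comparison of the two rules, followed by an illustration under assumed rates.

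**Inputs from the article.** 10 sessions per participant (3.3); 15 participants per arm (3.4). For sham, "For sham stimulation, the current will be ramped down to 0 mA directly after ramping up" (3.6), so the illustration is confined to the 15 active participants.

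**Rules.** Mark each of the 10 sessions severe or not severe, as if all 10 took place.
- Rule A (3.5): two adjacent severe sessions, or three or more in total.
- Rule B (3.13 read literally): one or more severe sessions.

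**Enumeration of all 2^10 = 1,024 patterns.**

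| Severe sessions | Patterns | Rule A met | Rule B met | Rules differ |
|---|---|---|---|---|
| 0 | 1 | 0 | 0 | 0 |
| 1 | 10 | 0 | 10 | 10 |
| 2 | 45 | 9 (adjacent pairs) | 45 | 36 |
| 3 or more | 968 | 968 | 968 | 0 |

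The rules differ in 10 + 36 = 46 patterns. In every one, Rule B is met and Rule A is not. The reverse never occurs, so Rule B taken literally leaves Rule A with nothing to decide. The 46 counts possibilities and says nothing about how likely they are.

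**Illustration with independent sessions.** The per-session severe-event probability p is an assumption.
- Rule B: 1 − (1−p)^10
- Rule A: 1 − (1−p)^10 − 10p(1−p)^9 − 36p²(1−p)^8

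At p = 0.01, Rule B gives 1 − 0.90438 = 9.56%. Rule A gives 1 − 0.90438 − 0.09135 − 0.00332 = 0.09% (0.094% before rounding).

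| Assumed p | Rule A | Rule B | Expected stops among 15, A | Expected stops among 15, B |
|---|---|---|---|---|
| 0.005 | 0.023% | 4.89% | 0.003 | 0.73 |
| 0.01 | 0.094% | 9.56% | 0.014 | 1.43 |
| 0.02 | 0.393% | 18.29% | 0.059 | 2.74 |

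**Illustration with events clustered within people.** Let the rate vary between people as a beta distribution with mean m and intraclass correlation ICC (both assumed). A given pattern with k severe sessions then has probability B(a+k, b+10−k)/B(a, b), where a = m(1−ICC)/ICC, b = (1−m)(1−ICC)/ICC and B(·,·) is the beta function. Summing over the patterns that meet each rule and multiplying by 15:

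| m | ICC | Expected stops, A | Expected stops, B |
|---|---|---|---|
| 0.01 | 0.1 | 0.15 | 1.02 |
| 0.01 | 0.3 | 0.23 | 0.64 |
| 0.02 | 0.1 | 0.32 | 1.97 |
| 0.02 | 0.3 | 0.47 | 1.25 |

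**Visit 10 losses through 3.5.** These need Rule A to be met within sessions 1 to 9. Over nine sessions there are 9 single-event patterns and 36 − 8 = 28 non-adjacent pairs, so the independent-session probability is 1 − (1−p)^9 − 9p(1−p)^8 − 28p²(1−p)^7. Times 15, this is 0.003, 0.012 and 0.051 at p = 0.005, 0.01 and 0.02. The clustered model gives 0.13 to 0.43 over the four settings above.

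**The case against.** A reader might infer that the two sections issue opposite mandatory orders. The text does not support that. Section 3.5 gives a sufficient condition for ending participation and orders nothing below its count, so it never requires a participant to continue. Both sections are obeyed by stopping at the first severe event.

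There is also a natural reading with no conflict: 3.13 is a short list of reasons, several of its other items carry no threshold either, and 3.5 supplies the working definition for this one. The count for missed sessions in 3.13 is weak evidence against that reading, because that limit appears nowhere else and had to be given there. This objection stands against calling it a contradiction. It does not remove the ambiguity: under the literal reading the 3.5 count has no effect, and under the shorthand reading 3.13 is incomplete as printed.

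On the second limb, a reader might infer that the plan discards the Visit 10 data of everyone who stops early. The article does not say so. It is silent on assessments after termination, which a condensed article may leave to the full protocol, and discontinuation in 3.13 may mean treatment only. What stands is narrower: 3.5 itself uses the wider word directly after a sentence about stimulation.

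On size, every rate and ICC above is assumed, and the article describes the known side effects as limited (section 4).

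**Conclusion.** The point holds as an unreconciled stopping threshold, and it is a cheap improvement rather than a serious flaw. The certain part needs no assumed rate: the literal rules part company after one severe session or two non-consecutive ones, and there only 3.13 applies. How many participants this touches cannot be fixed from the article. Under the assumed rates, the gap between the two readings in the active arm runs from about 0.4 participants (0.64 − 0.23, clustered) to about 2.7 (2.74 − 0.06, independent). In an arm of 15, the upper part of that range would visibly move a withdrawal rate.

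The participation wording is the lesser point. It probably costs fewer than one Visit 10 assessment, and only if it is applied literally. It does not by itself threaten the primary imaging comparison.

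**What to change.** 1. Have 3.13 refer to the session count in 3.5, or state a single rule used by both sections. Which threshold to adopt is the investigators' clinical choice.
2. Reword 3.5 so that meeting the threshold stops stimulation, while the already scheduled Visit 10 HAM-D-17 and QIDS-SR-16 are still collected, together with the MRI where it is safe and the participant consents.

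The cost is a short amendment and the already planned Visit 10 assessments for the few who stop early. No extra participants, visits or instruments are needed.
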